**Fig. 2 Fig2:**
[figure not shown]
Clinical trial overview. CT Computed tomography, *CT group* Active comparator arm in which procedures are carried out guided by conventional computed tomography, *NAV group* Experimental arm of the trial in which procedures are carried out using navigation assistance

**Fig. 3 Fig3:**
[figure not shown]
Participant timeline

For every procedure, a clinical research assistant (CRA) is present with responsibility for recording the patient data in the eCRFs and later integrating the relevant medical reports (e.g., consultation, radiology, anatomopathology, hospital discharge summary reports) after they have been anonymised. All data recorded for a patient are validated by the radiologist who carried out the procedure. To minimise errors, the eCRFs were designed using range checks (to verify that entered values are within defined boundaries) and conditional logic (request/prevent entry of a field if the preceding answer is yes/no). Furthermore, during the period of patient enrolment, a data manager will verify the coherence of the data recorded and request that corrections be made when necessary. All data are monitored by Grenoble-Alpes University Hospital (trial sponsor) in order to control the occurrence of AEs and to verify that for every patient enrolled there is a signed consent certificate and that the inclusion and exclusion criteria were respected. In addition, the data included in the eCRF of every enrolled patient will be verified exhaustively. All recorded data are anonymous; only the principal investigator of each centre has access to the list of participants enrolled in his/her centre.

The trial is evaluated according to the previously stated primary and secondary outcomes whose aim is to evaluate the clinical benefit of the navigation system. The primary outcome, a combined criterion composed of three criteria to assess the safety, efficacy and performance of navigation-assisted procedures, is evaluated as follows:
*Safety*: The number of AEs that are considered to be major (i.e., classified as C, D, E or F according to the scale defined by the SIR) and are attributable to the needle insertion phase of the procedure
*Efficacy*: The number of targets reached; the target is considered to have been reached when the needle is positioned accurately enough to allow the next step of the procedure to be carried out
*Performance*: The number of control scans acquired during the needle insertion phase of the procedure; that is, the number of scans acquired between and including H1 (time of the first CT scan on which the needle is visible) and H2 (time at which the needle has reached the target)

The secondary outcomes are used to assess the time required to reach the target (H2 − H1), the satisfaction of the operator with the procedure (quantitative scale) and the radiation dose delivered during the needle insertion phase of the procedure (radiation delivered between and including H1 and H2). Furthermore, because it is expected that the navigation system will provide a greater clinical benefit for difficult procedures compared with standard procedures, a subgroup analysis according to the expected difficulty of the procedure will be carried out. The usability of the device is also evaluated by analysis of the needle holder localisation files generated during the procedures.

To minimise ascertainment bias, the CT scans are post-processed before analysis such that it cannot be determined whether the scans were acquired in the experimental or comparator arm. For scans acquired with navigation assistance, the needle holder, the portion of the needle outside the body and the transmitter are erased. For scans acquired under conventional CT guidance, the portion of the needle outside the body is erased.

For each enrolled patient, the primary outcome is determined by a blinded evaluation of the post-processed CT scans and the patient’s medical reports (procedure report and hospital discharge summary), as previously described. The evaluation is carried out by a trained radiologist blinded to the patient group and to all evaluations made by the investigating radiologist who carried out the procedure. In case of discordance between the data entered by the evaluating radiologist and the investigating radiologist, the discordance is presented to an expert committee by the CRA responsible for centre and data management. The expert committee is composed of two senior radiologists who are independent from the evaluating and investigating radiologists and who will provide a consensus in case of discordance.

To ensure the correct progress of the trial and to verify that the proposed statistical analysis framework is appropriate, an interim analysis of the primary outcome will be performed once the first four participating hospitals have finished patient enrolment. To maintain a global cut-off of 5% for the final analysis, the interim analysis will be carried out using a cut-off of 0.1%. The results of the interim analysis will be considered by the TSC to judge whether the statistical analysis framework requires modifying. When patient enrolment is finished, the final monitoring is completed and the coherence of the recorded data is verified, the database will be frozen, and the final statistical analysis of the data will be carried out.

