**Methods/design:**

This study is designed as an open, multicentre, prospective, randomised, controlled interventional clinical trial and is structured as a standard two-arm, parallel-design, individually randomised trial. A maximum of 500 patients will be enrolled. In the experimental arm (navigation system), the procedures are carried out using navigation assistance, and in the active comparator arm (CT), the procedures are carried out with conventional CT guidance. The randomisation is stratified by centre and by the expected difficulty of the procedure. The primary outcome of the trial is a combined criterion to assess the safety (number of serious adverse events), efficacy (number of targets reached) and performance (number of control scans acquired) of navigation-assisted, CT-guided procedures as evaluated by a blinded radiologist and confirmed by an expert committee in case of discordance. The secondary outcomes are (1) the duration of the procedure, (2) the satisfaction of the operator and (3) the irradiation dose delivered, with (4) subgroup analysis according to the expected difficulty of the procedure, as well as an evaluation of (5) the usability of the device.

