For this trial, a maximum of 500 patients for whom a percutaneous procedure in the thoraco-abdominal area under CT guidance has been prescribed will be enrolled in the study across the nine participating hospitals. The trial is structured as a standard two-arm, parallel-design, individually randomised trial*.* Patients are randomly assigned to the experimental arm of the trial in which procedures are carried out using navigation assistance (the NAV group), where the procedures are carried out using navigation assistance supplied by the medical device under evaluation (IMACTIS-CT®), or to the active comparator arm of the trial in which procedures are carried out guided by conventional CT (CT group), where the procedures are carried out under conventional CT guidance. The randomisation is stratified by centre and by the expected difficulty of the procedure. The assignment is open label for both the radiologist and patient.

Because a previous clinical trial has already demonstrated improved needle placement accuracy in navigation-assisted procedures using the IMACTIS-CT® device (4.1 mm [2.7–9.1]) compared with conventional procedures (8.9 mm [4.9–15.1], *p* < 0.001) according to ITT analysis [29], the aim of this trial is therefore to evaluate the clinical benefit of the navigation system. The primary outcome is a combined criterion composed of three different criteria which assess, respectively, the safety, efficacy and performance of navigation-assisted CT-guided procedures by comparing the results obtained in the navigation-assisted group with those obtained in the conventional group. The criteria will be evaluated by a blinded expert committee. It will be determined that the navigation system represents a clinical benefit if non-inferiority in terms of safety, efficacy and superiority in terms of performance is obtained in the navigation-assisted group with respect to the conventional group. Also evaluated, in terms of secondary outcomes, are (1) the duration of the procedure, (2) the satisfaction of the operator and (3) the irradiation dose delivered, with (4) subgroup analysis according to the expected difficulty of the procedure, as well as an evaluation of (5) the usability of the device.

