Once the patient has been assigned to the CT or NAV group, the procedure prescribed can be carried out. For patients assigned to the CT group (procedures carried out under conventional CT guidance), the ideal needle path trajectory is defined on the acquired CT scan using the CT console. The needle entry point is identified and marked on the patient’s skin, and the sterile area is set up. A local anaesthetic is administered, and the radiologist carries out the procedure, iteratively verifying the correct position of the needle by acquiring control scans until the target has been reached. A final control scan is acquired that shows the position of the needle at the target before the procedure is continued to carry out the prescribed gesture (e.g., biopsy, abscess drainage). Any further control scans acquired after the ‘final control scan’ are not counted for this study.

For patients assigned to the NAV group (procedures carried out using navigation assistance supplied by IMACTIS-CT®), first the navigation system is installed beside the CT scanner and connected to the network. The system can then be started up, followed by the software. The electromagnetic receiver is attached to the non-sterile needle holder, and the images of the acquired CT scan are automatically transferred to the navigation system via the network. Automatically, the arrival of the images is detected, the coherence of the series is verified and the registration of the images is carried out. The navigation system enables the radiologist to define the ideal needle path trajectory directly on the patient by using the needle holder to navigate within the acquired CT volume. Once the ideal trajectory has been defined, the entry point is marked on the patient’s skin, and the sterile area is set up. The navigation system is then made sterile by removing the electromagnetic receiver from the non-sterile needle holder, placing the receiver in a sterile cover, and attaching it to the sterile needle holder. A local anaesthetic is then administered, and the radiologist carries out the procedure using navigation assistance until the target has been reached. Control scans can be acquired at any moment. A final control scan is acquired that shows the position of the needle at the target before the procedure is continued.

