## Discussion

Navigation assistance systems have demonstrated their value in the fields of orthopaedics, urology and neurosurgery. A previous clinical trial demonstrated that use of the IMACTIS-CT® navigation system during CT-guided interventional procedures improved needle placement accuracy significantly and reduced the number of control CT scans acquired. The aim of the present trial is to address the lack (to the best of our knowledge) of published high-level evidence studies involving evaluation of navigation-assisted, CT-guided interventional procedures. The trial is designed to evaluate the clinical benefit, in terms of safety, efficacy and performance, of navigation-assisted, CT-guided procedures. It is expected that the more accurate needle placement achieved using the navigation system will decrease the procedure duration and decrease the radiation exposure delivered. This trial is important because it addresses the problems associated with conventional CT guidance—inaccurate needle placement, radiation exposure—and is particularly relevant because the number of interventional radiological procedures carried out in routine clinical practice is increasing.

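### The outcome named procedure duration starts at the first CT scan showing the needle, an event whose timing depends on the arm, so the comparison may favour navigation

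*Protocol article*

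**What the plan says.** The Abstract and Study design and setting both list "the duration of the procedure" first among the secondary outcomes. The Methods subsection then gives the measurement: the outcome is "used to assess the time required to reach the target", calculated as H2 − H1. The two time points are defined with the performance criterion in the same subsection. H1 is the "time of the first CT scan on which the needle is visible" and H2 is the "time at which the needle has reached the target". No other duration measure is described.

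The Methods subsection also sets out the workflow of each arm after randomisation. CT-arm operators verify needle position iteratively with control scans. NAV-arm operators work under navigation, and "Control scans can be acquired at any moment"; the only scan described as a set step is the final one with the needle at the target. The Materials subsection confirms that the needle's progress is visible in real time during insertion.

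The Discussion expects the system to "decrease the procedure duration".

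**The concern.** A duration outcome in a randomised comparison needs a clock that starts at the same kind of event in both arms. Here the start is a scan, and the device is meant to reduce scanning: the Statistical analysis section plans for 20% fewer control scans. An arm that scans later starts its clock later, whatever the true speed of insertion.

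Two kinds of time drop out. The first is needle advance before the first scan, which is part of reaching the target by any ordinary reading. The second is preparation that exists only in NAV. If H2 − H1 came out shorter in NAV, the report could present this as a shorter procedure when the whole procedure had taken as long or longer. Part of the apparent saving would also restate the scan-count result rather than add separate evidence.

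**Working it through.** The plan states no expected duration or standard deviation, so there is no figure to reproduce. The check sets the definitions beside the workflow, then illustrates how the clock behaves.

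**Step 1. What falls before H1 after randomisation (Methods subsection).**

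| Step | NAV | CT |
|---|---|---|
| Station installed, connected, started | yes | no |
| Image transfer and registration | yes | no |
| Trajectory planning | with needle holder | on CT console |
| Entry point marked, sterile area, local anaesthetic | yes | yes |
| Receiver moved to sterile cover and holder | yes | no |
| Needle advance before first scan | possible, under real-time display | possible, until first check scan |

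The transmitter is attached before randomisation in every patient, so it does not separate the arms. Three rows are NAV-only, and none is counted.

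**Step 2. How the recorded time depends on scanning.** Let T be the true insertion time, n the number of scans from H1 to H2 inclusive, and t the spacing between scans. Assume the last scan marks H2. Then

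recorded time = (n − 1)t, and uncounted insertion time = T − (n − 1)t.

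The Background reports per-protocol median scan counts from the previous trial of 2 (NAV) and 3 (CT). Using these, and assuming the same counting convention and the same true time T = 3t in both arms:

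- NAV: recorded (2 − 1)t = t; uncounted 3t − t = 2t.
- CT: recorded (3 − 1)t = 2t; uncounted 3t − 2t = t.
- Ratio NAV/CT = t/2t = 0.5, with no true difference.

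**Step 3. How far this depends on the assumptions.** T is kept equal in both arms.

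- Scans spread evenly over insertion, the first at T/n and the last at T: recorded time = T(n − 1)/n. This gives T/2 in NAV and 2T/3 in CT, a ratio of (1/2)/(2/3) = 0.75.
- First scan at needle entry in both arms: recorded time = T in each, a ratio of 1.
- First scan at needle entry in NAV only, with CT as in Step 2: 3t/2t = 1.5.

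With identical true times, the recorded ratio runs from 0.5 to 1.5 across these cases, solely through when the first scan is taken. The last case is allowed by the text but is less in keeping with a system meant to replace check scans.

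**Step 4. The single-scan case.** If H2 is taken as a scan time and n = 1, recorded time = (1 − 1)t = 0. This holds in either arm.

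**The case against.** The best defence is scope. The Abstract says the trial evaluates benefit during needle insertion, and attributable adverse events, scan count and radiation dose are all confined to that phase. The formula for the time outcome is stated openly. On this view, leaving out set-up is deliberate and only the label is loose. That explains the missing set-up time. It does not repair the start point, because needle advance before the first scan is itself insertion.

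It is also fair that the CT arm has uncounted time before H1: console planning, marking, sterile preparation, anaesthesia and any advance before the first check. The outcome plays no part in the clinical-benefit rule or the sample size, and the Discussion's remark about duration is an expectation, not a planned conclusion.

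A reader might go further and infer three things that the documents do not support.

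- That the measure is shown to favour NAV. NAV scans may be taken early or late, and the first CT-arm scan has no fixed time, so the direction is an inference from the workflow.
- That every single-scan NAV case records zero minutes. This holds only if H2 is that scan's time, which the definition of H2 does not say, and it would apply equally to CT. The previous trial's lower quartile was 2 scans in both arms, so under the same counting convention such cases would be a minority.
- That a known number of minutes is lost. No times are given; a figure such as 5–15 minutes for set-up plus navigation before the first scan would be pure assumption.

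**Conclusion.** The point holds in a limited form. The outcome's name promises the whole procedure, while its measurement starts at a scan whose timing depends on the arm and leaves out preparation that exists only in NAV. H2 − H1 may therefore favour NAV and is partly tied to the scan count. The illustration shows that an apparent halving is possible with no true difference, but it rests on assumed equal insertion times, an assumed scan spacing, the last scan marking H2, and the previous trial's medians and counting convention carrying over. The real size cannot be computed from the documents.

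This affects the interpretation of one secondary outcome, not the primary conclusion. It should be corrected because the definition is explicit and a claim of shorter procedures could rest on it.

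**What to change.** Define procedure duration as the time to H2 from an event that every patient reaches before the arms diverge: the initial CT scan, or randomisation if its time is retained. Keep H2 − H1 as a supportive measure labelled 'time from first needle scan to target', and state that no reduction in procedure duration will be claimed from it. State also whether H2 is read from a scan, so that the handling of single-scan cases is clear in both arms.

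The cost is a change of outcome wording and one added derived variable. There are two drawbacks. The new duration includes preparation and trial-only steps (with the initial scan as the start: the difficulty rating, eCRF entry and randomisation), so it will be more variable and less sensitive to a difference in insertion time. The sponsor must also confirm that the start timestamps are available; the article does not say that a randomisation time is recorded. If neither start time can be recovered, the minimum change is to rename the outcome and drop any statement about procedure duration.

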An initial CT scan of the patient is acquired before assignment of the patient into the experimental or comparator arm of the trial. First, landmarks are made on the patient’s skin using metal wire or a metal grill (required for conventional CT guidance), and the electromagnetic transmitter of the navigation system is attached to the patient’s skin (required for navigation-assisted CT guidance). The CT scan is then acquired, and it is verified that the procedure originally prescribed is maintained and that the navigation system is available and working. If the originally prescribed procedure is no longer maintained or the navigation system is not available or not working, the patient is removed from the study, and the procedure is carried out under conventional CT guidance.

Otherwise, the radiologist estimates the expected difficulty of the procedure on the basis of the initial CT scan. A procedure is expected to be difficult if the needle path is on a plane that is oblique to the acquired axial images, the target moves with respiration, the procedure is a lung biopsy, the target is difficult to reach (due to small size or depth of location) or the needle path is very narrow. Difficult interventions are associated with an increased risk of major complications and of procedure failure and also with an increase in the number of control scans required compared with standard interventions. Because these risks have a direct impact on the three criteria that constitute the primary outcome of the study, respectively, safety, efficacy and performance, the random assignment of the patient into the experimental or comparator arm of the trial is stratified by the expected difficulty of the procedure as well as by centre.

The expected difficulty of the procedure is entered into the electronic case report forms (eCRFs) provided by Medsharing (Fontenay Sous Bois, France; www.medsharing.fr), and the patient is then randomly assigned to the experimental (NAV) or comparator (CT) arm of the trial. The randomisation lists are generated by Medsharing using a randomisation by minimisation algorithm. By acquiring the CT scan before randomisation, it can be verified that the originally prescribed procedure is maintained and that the navigation system is available and working before the patient is assigned to the CT or NAV group, thereby minimising the later imputation of missing data for the statistical analysis.

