The trial does present certain limitations, however. Firstly, the operators are not stratified according to experience, reducing the comparability of the results in the two groups. However, because the patients are randomly assigned to the experimental or comparator arm, and considering the small number (two to five) of investigators participating in the study per centre, it is expected that the distribution of experienced operators is comparable in both groups. Furthermore, training is provided for the participating radiologists and is obligatory before authorisation is granted to carry out a navigated procedure on a patient enrolled in the trial. Another limitation is that the assignment to the experimental or comparator arm is open label for the radiologist. The assignment cannot be made double-blind, owing to the nature of the procedure. However, the criteria of the primary outcome will be evaluated by a blinded expert committee after the CT scans have been post-processed, such that it cannot be determined whether the scans were acquired in the experimental or comparator arm. A third limitation concerns the absence of respiratory motion tracking integrated into the navigation system; a breath-hold approach is therefore required for certain procedures (e.g., lung procedures). An interesting future perspective is therefore the development and inclusion of respiratory motion management into the system, which is expected to improve the system’s accuracy. Finally, because the navigation system was designed to assist CT-guided interventional procedures, the system has no multi-modal capability.

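### The procedures described do not secure blinding of the primary-outcome evaluation, because the evaluator reads the procedure report and only anonymisation of reports is described

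*Protocol article*

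**What the plan says.** All of this comes from the protocol article.

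- **Evaluator's material** (Methods/design, Methods, after Fig. 3): the primary outcome is determined from post-processed CT scans and the "medical reports (procedure report and hospital discharge summary), as previously described".
- **Blinding claimed** (same paragraph): the evaluating radiologist is "blinded to the patient group and to all evaluations made by the investigating radiologist who carried out the procedure".
- **Handling of reports** (Methods, data recording): a clinical research assistant (CRA) adds the medical reports to the eCRF "after they have been anonymised". No removal of arm, device or guidance wording is mentioned.
- **Handling of images** (Methods): scans are processed "such that it cannot be determined whether the scans were acquired in the experimental or comparator arm". For navigation scans the holder, the outer needle and the transmitter are erased. The conventional arm has a shorter list: "For scans acquired under conventional CT guidance, the portion of the needle outside the body is erased".
- **Transmitter** (Methods, initial scan): before the pre-randomisation scan, "the electromagnetic transmitter of the navigation system is attached to" the skin of every patient who goes on to randomisation.
- **Discordances** (Methods): where evaluator and operator differ, "the discordance is presented to an expert committee by the CRA responsible for centre and data management".
- **Who evaluates**: the Abstract and Methods describe one blinded radiologist, with a committee for discordant cases. Study design and setting names a blinded expert committee as evaluator, and the Discussion says "the criteria of the primary outcome will be evaluated by a blinded expert committee after the CT scans have been post-processed".

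**The concern.** The trial is open label for operator and patient, so the credibility of the primary outcome depends on the independent reading. The article describes in detail how images are masked. It then gives the evaluator a document written by the unblinded operator and describes no masking of arm in it. A report of the procedure would normally say how the needle was guided, whether the target was reached and what went wrong. Those are the group and the operator's evaluations that the evaluator is supposed not to know.

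The three criteria are not equally exposed. Whether a major adverse event was directly caused by needle insertion, and whether the needle was placed accurately enough for the next step, are judgements. They feed the safety and efficacy non-inferiority tests. The count of scans between H1 and H2 is closer to objective.

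There is also an effect on the safeguard. The committee acts only when evaluator and operator disagree. An evaluator who has read the operator's account is more likely to agree with it, so a doubtful case may never reach the committee.

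**Working it through.** The plan gives no figure on this point to reproduce. The check is mainly a comparison of statements, followed by an illustration of what is at stake.

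**1. Reports against the blinding claim.** The procedure report is a named input to the evaluation. The evaluator must not know the group or the operator's evaluations. The one processing step described for reports, anonymisation, concerns patient identity. Followed as written, the two requirements conflict unless a redaction step exists that the article does not describe.

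**2. Image masks.** The transmitter is on the erasure list for navigation scans only, although every randomised patient wears it at the initial scan. Whether this reveals the arm depends on facts that are not given:
- Transmitter removed from CT-group patients after randomisation: their control scans contain none, and the two lists are adequate.
- Transmitter left on in the CT group: a visible transmitter would mark a conventional procedure.
- Initial scan shown unprocessed in both arms: the transmitter appears in both and reveals nothing.
- Initial scan shown but processed only in the navigation arm: it would reveal the arm.

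The initial scan precedes randomisation, lies outside the H1–H2 count and is not said to be shown to the evaluator. This limb therefore stays open.

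**3. Discordance step.** A CRA attends every procedure, and the CRA responsible for the centre presents discordances. The article does not say that they are the same person, nor that the arm is withheld when the case is presented. The Methods call the committee members independent; that section does not call them blinded.

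**4. Who evaluates.** Abstract and Methods: one radiologist, committee for discordance only. Study design and setting, and Discussion: a blinded committee evaluates the criteria. The Discussion uses the committee version to answer the open-label limitation, so the difference matters.

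**5. Illustration for safety.** Inputs from the article: margin 7%, initial rate 5%, threshold 12%, at least 200 patients per group, 90% two-sided confidence interval (1.645). Assumption: the true rates are 12% with navigation and 5% with conventional guidance, so the difference equals the margin (12% − 5% = 7%). A share f of navigation-arm events is wrongly judged not attributable, net of any correction by the committee.

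Observed navigation rate p = 0.12 × (1 − f). SE = √((p(1 − p) + 0.05 × 0.95)/200). z = (0.07 − (p − 0.05))/SE − 1.645. False non-inferiority rate = Φ(z).

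| f | p | SE | z | False non-inferiority |
|---|---|---|---|---|
| 0 | 0.120 | 0.0277 | 0 − 1.645 = −1.645 | 5% |
| 1/8 | 0.105 | 0.0266 | 0.015/0.0266 − 1.645 = −1.08 | about 14% |
| 1/4 | 0.090 | 0.0254 | 0.03/0.0254 − 1.645 = −0.47 | about 32% |

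Of 0.12 × 200 = 24 expected navigation-arm events, f = 1/4 means 6 and f = 1/8 means 3. The 1/8 row also represents a one-quarter shift of which the committee reverses half.

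**The case against.** A reader might infer that the evaluation is simply not blind. The article does not show that. It states blinding as a requirement directly after naming the reports, and how reports are prepared to meet it is operational detail that a full protocol could hold. That the report names the guidance method is a reasonable expectation, not a documented fact. The sentence on anonymisation concerns entry into the eCRF and does not say that nothing else is done. This stands, and it limits the point to blinding not being secured by what is described. It does not remove the point, because the text names an input that would defeat the blinding it claims.

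A reader might also infer that the transmitter gives away the arm, or that a CRA who attended the procedure informs the committee. Neither is supported. The transmitter matters only under some of the readings set out above, and the presenting CRA is not said to be the one who attended. Both are matters to clarify.

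The illustration is open to attack as well. The one-quarter shift has no source. If the evaluator alone drops an event that the operator called attributable, that is a discordance and goes to two independent senior radiologists. The shift arises only if the operator judged the same way or the committee agrees. The objection is right that the 32% is not an estimate of what this design will produce.

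**Conclusion.** The point holds in limited form: the described procedures do not secure blinding of the primary-outcome evaluation. The firm ground is the procedure report, which is given to the evaluator with no described masking of arm or of the operator's assessments. The inconsistency about who evaluates is also real. Safety attribution and target reached are exposed; the scan count is less so.

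The size of any bias cannot be derived from the article. The range of 5% to about 32% holds only for true rates at the safety margin, 200 patients per arm, and an assumed net loss of none to a quarter of navigation-arm events after the discordance step. The conclusion assumes that reports have ordinary content and that the full protocol, which is not shown, contains no redaction step. If it does contain one, the remedy for the reports is to say so in the text. The change should be made, but the point does not show that the results are biased.

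**What to change.** 1. Before evaluation, redact from procedure reports and discharge summaries the guidance method, any device wording, and the operator's own assessments of target and attribution. Keep the clinical facts needed to classify an event.
2. Apply one identical mask to both arms, on every scan the evaluator is shown: erase everything outside the skin. This settles the transmitter question without needing to know whether it stays on in the CT group.
3. Send discordances to the committee as two unlabelled readings on masked material, and state that the committee is blinded.
4. Align Study design and setting and the Discussion with the Abstract and Methods: one blinded radiologist evaluates, and the committee resolves discordances.

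Cost: a few minutes of redaction per report, the same image processing run on both arms, and a small risk that redaction removes useful clinical context. Cases already read can be read again on redacted material.
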